### 2.2. Study Population

Healthy postmenopausal women from the general public residing in the Hunter region of New South Wales were invited to participate following expressions of interest to approved newspaper and radio campaigns. Each volunteer was first provided with an information statement outlining the study objectives and procedures. A health and lifestyle questionnaire that collected information pertaining to their menopausal status, medication and dietary supplement use and current perception of their cognitive status was completed by interested parties. Upon returning the questionnaire, a study investigator pre-screened volunteers via telephone to determine their potential suitability, as described in Table 1, and to invite them in for a screening/baseline visit at the research centre. They were also encouraged to consult with their medical practitioner regarding their intention to participate in this intervention prior to their first visit. Written informed consent was obtained at start of the screening/baseline visit.

Our power calculations (G*Power) [29] showed that 74 participants would give 80% chance of detecting a statistically significant difference (*p* < 0.05) of medium effect size (standardized difference = 0.67) in cognitive performance (composite score) between Resveratrol and placebo treatments. To allow for attrition, we aimed to recruit 80 women.

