### 2.3. Investigational Product and Allocation

The active and placebo capsules were of identical appearance and supplied by DSM Nutritional Products Ltd, Switzerland. The active capsule comprised 75 mg of 99% pure synthetic trans-resveratrol. The placebo comprised several inert excipients: calcium hydrogen phosphate, microcrystalline cellulose, prosolv 50 and hydrated magnesium silicate. Two hundred capsules were each dispensed in sealed white opaque containers and containers were identifiable only by code numbers. An independent investigator who held the code list allocated participants to each treatment group based on the minimisation method [30], to minimise differences between groups in age and years since ceasing menses (obtained from their health and lifestyle questionnaires) prior to the scheduled screening/baseline visit. The first participant was allocated randomly. Containers allocated to volunteers who were subsequently deemed ineligible or did not attend the screening/baseline visit were reassigned and the allocation list adjusted accordingly. Blinding will be maintained until all data analysis has been completed.

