### 2.4. Screening/Baseline Visit (Week 0)

Potentially eligible volunteers attended the 3-h screening/baseline visit after having refrained for at least an hour from medication, food or beverages other than water. Height, weight and waist circumference were measured followed by seated blood pressure (BP) readings to determine BP eligibility. Dementia status was then assessed using the Australian version of the Mini-Modified Mental State (3MS) examination. The 3MS is a widely used tool for screening suspected dementia; a score of less than 78 was considered impaired and necessitated exclusion from the study [31].

Those who met the eligibility criteria were fitted with a Transcranial Doppler (TCD) ultrasound headpiece to assess basal cerebral haemodynamics and CVR to both hypercapnic and cognitive stimuli bilaterally in the middle cerebral artery (MCA). Participant’s performances were also recorded during cognitive testing. At the conclusion of cognitive testing, participants underwent a hypercapnic assessment of CVR in the posterior cerebral artery (PCA). A physical function assessment was then carried out before a series of six paper-based questionnaires to assess mood and general wellbeing were completed to conclude the visit. Figure 1 depicts the flowchart of the participants who were enrolled in the study. It also highlights our study population size (*n* = 80, 40 per treatment group) indicating that our treatment target has been reached.

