### 2.14. Statistical Analysis

The primary outcome is the effect of resveratrol supplementation *versus* placebo on cognitive performance, determined using a composite score of all memory tests. Treatment by time effects will be determined by analysis of variance (ANOVA), or analysis of covariance (ANCOVA) in the event of interacting variables. the process of subject allocation by minimisation will have balanced age and years since cessation of menses between groups; however other baseline characteristics such as clinic BP, basal PI, BMI, 3MS score and years of education will be considered covariates if they were significantly correlated with the primary outcome.

Treatment changes in CVR to hypercapnia and/or cognitive stimuli, improvements in physical function, mood states and quality of life will be assessed using linear regressions with false rate discovery adjustments used to minimise type 1 error. In addition, to explore the potential benefits of early intervention, the magnitude of improvement following resveratrol supplementation will be compared in early (<10 years) and late (>10 years) postmenopausal women. Statistical significance for the primary outcome is set at *p* < 0.05 and false discovery rate will be applied to secondary outcomes. Statistical analyses will be performed using SPSS version 21.0 (SPSS by IBM Inc., Chicago, IL, USA).

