## 3. Conclusions

We have identified postmenopausal women as a vulnerable population at increased risk of cognitive decline and dementia who may benefit from supplementing their diet with resveratrol. This paper provides a rationale for investigating the effects of resveratrol supplementation on cognitive performance and mood in postmenopausal women based on our hypothesis that resveratrol can augment both by enhancing cerebrovascular perfusion. According to our hypothesis, any improvements in cognition will be secondary to improvements in CVR; however, the technical limitations of obtaining reliable TCD ultrasound signals, particularly in older women, did not warrant the inclusion of cerebrovascular function as the primary outcome as recruitment may be limited. Nonetheless it provides a detailed study design and protocol for undertaking this investigation, utilising TCD as a novel approach to evaluate impacts of supplementation on CVR. Additionally, through this paper we have outlined a model approach for which we can establish a portfolio of evidence for the efficacy of not only resveratrol but other vasoactive nutrients in maintaining optimal circulatory function to ameliorate the risk of developing dementia.

Given that resveratrol supplements are readily available over-the-counter to consumers, the anticipated outcomes will offer a non-pharmaceutical approach for managing menopause-related symptoms and counteracting accelerated cognitive and physical decline as well as mood disorders in women postmenopausally, which can be readily implemented by clinicians and the public.

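### Balance from minimisation is given as the reason to leave age and years since menses out of the model; it is a reason to include them, though the loss may be small in a change analysis

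*Protocol article*

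**What the plan says.** Section 2.3 states that an independent investigator allocated participants by minimisation, "to minimise differences between groups in age and years since ceasing menses". Both values came from the health and lifestyle questionnaire, before the baseline visit.

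Section 2.14 plans a treatment-by-time ANOVA for the primary composite score, or ANCOVA if there are interacting variables. It then says that "the process of subject allocation by minimisation will have balanced age and years since cessation of menses between groups; however other baseline characteristics" (clinic BP, basal PI, BMI, 3MS score and years of education are named) will be considered as covariates if they correlate significantly with the primary outcome. Nothing in the article puts age or years since menses into any model.

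On size, section 2.2 says that "74 participants would give 80% chance of detecting a statistically significant difference" of "medium effect size (standardized difference = 0.67) in cognitive performance (composite score"), and adds: "To allow for attrition, we aimed to recruit 80 women". Section 2.4 gives "40 per treatment group". For the Doppler outcomes, the Conclusions mention "the technical limitations of obtaining reliable TCD ultrasound signals, particularly in older women".

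**The concern.** Minimising on a prognostic factor removes most of that factor's contribution to the between-arm difference, so the true variance of the estimated treatment effect falls. A model without the factor still counts its variance as residual error. The reported standard error is then larger than the true one, the confidence interval is too wide, and the test rejects less often than its nominal level. Balance by design therefore argues for adjustment.

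The section also applies two different tests. Other characteristics may enter if they are related to the outcome. The two allocation factors are set aside on a different ground, presumed balance. Read literally, BMI could enter while age stays out, even if age were the strongest correlate.

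At stake are some precision and power in a small trial, and agreement between the primary p-value and its stated level. For cerebrovascular responsiveness (CVR), the rationale is weaker still, because balance among all randomised women need not hold among those with a usable signal.

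**Working it through.** **Inputs from the article.** "Statistical significance for the primary outcome is set at *p* < 0.05" (two-sided assumed; sidedness is not stated). Standardised difference d = 0.67. 74 evaluable women, 37 per arm. Minimisation on two factors.

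**Input not in the article.** R², the share of variance of the *analysed* outcome explained by age and years since menses. It is assumed below over a range.

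**1. The plan's own figure.** Two-sample t test, noncentrality d × √(n/2) = 0.67 × √(37/2) = 2.88, 72 df. Power is 81.1% at 74 women. The smallest total reaching 80% is 72. The stated 74 is reproduced, and the calculation takes no credit for covariates.

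**2. Size by formula.** With the factors balanced, the unadjusted standard error is too large by 1/√(1 − R²). Under perfect balance and a normal approximation, the true type I error is 2 × [1 − Φ(1.96/√(1 − R²))]. Adjusted power uses d/√(1 − R²) with 70 df.

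| R² | SE too large by factor | Type I error, unadjusted | Power, adjusted |
|---|---|---|---|
| 0 | 1.00 | 5.0% | 81.1% |
| 0.05 | 1.03 | 4.4% | 83.0% |
| 0.10 | 1.05 | 3.9% | 85.0% |
| 0.20 | 1.12 | 2.8% | 88.8% |
| 0.30 | 1.20 | 1.9% | 92.5% |

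**3. Size by simulation.** Real minimisation does not balance perfectly. Settings: 74 women, minimisation on banded age and banded years since menses, always to the arm that reduces imbalance, 5,000 runs per setting. Monte Carlo standard error is √(0.05 × 0.95/5000) = 0.3 points for type I error and about 0.5 for power.

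| R² | Type I error, unadjusted / adjusted | Power, unadjusted / adjusted | Power difference |
|---|---|---|---|
| 0 | 5.1% / 4.9% | 81.1% / 80.8% | −0.3 |
| 0.05 | 4.7% / 5.1% | 81.8% / 82.3% | 0.5 |
| 0.10 | 4.0% / 5.0% | 82.6% / 84.6% | 2.0 |
| 0.20 | 3.0% / 4.9% | 83.3% / 88.4% | 5.1 |
| 0.30 | 2.4% / 5.2% | 85.6% / 92.3% | 6.7 |

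At R² = 0.20 the estimate's actual SD is 0.211. The unadjusted model reports 0.231 and the adjusted model 0.209. With the favoured arm chosen only 80% of the time, the power differences at R² = 0.10, 0.20 and 0.30 are 2.1, 5.4 and 7.8 points. A further independent run at R² = 0.20 gave a type I error of 3.6% unadjusted against 5.5% adjusted, and power of 82% against 87%.

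**4. The planned analysis.** With assessments at weeks 0 and 14 only, a treatment-by-time test is a comparison of change scores. An age effect on the level of cognition that is the same at both visits cancels. Simulation with 74 women, 4,000 runs, an assumed test-retest correlation of 0.7, and the factors acting on level only:

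| Share of level explained | Type I error on change, unadjusted / adjusted | Power at 0.67 SD of change, unadjusted / adjusted |
|---|---|---|
| 10% | 5.0% / 5.0% | 81.2% / 80.7% |
| 20% | 4.9% / 4.9% | 80.2% / 80.0% |
| 30% | 5.5% / 5.4% | 81.4% / 81.0% |

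Nothing is lost here. With the baseline score as covariate, unadjusted type I error is 4.7%, 4.7% and 4.5%. It falls to 4.0%, 3.5% and 2.4% only if week-14 scores are analysed without baseline, which the article does not plan.

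**The case against.** The strongest objection is step 4. The article's evidence that age matters concerns level: section 2.10 says executive function declines with age. No passage shows that age or years since menses predicts 14-week *change*. The early-versus-late comparison in section 2.14 suggests the authors think benefit may vary with time since menopause, but it is exploratory and gives no figure. This objection stands: the size of the loss in the planned test is unknown and may be nil.

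Exclusion is also inferred from a contrast rather than stated, and the ANCOVA clause leaves some room. That is fair. But the sentence gives a reason for setting the two factors aside, and the reason is wrong whatever a fuller plan adds. The article also does not say how strictly the minimisation was run. Containers were reassigned when volunteers proved ineligible, so achieved balance, and with it the mismatch in standard errors, may be weaker than simulated.

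Three stronger readings are tempting and not supported:
- **The primary test is invalid.** Any error is conservative. Type I error is not inflated and the estimate is not biased.
- **The trial is underpowered.** Unadjusted power at 74 women is 81.1% by formula and 82.6% to 85.6% in the step 3 settings with R² from 0.10 to 0.30.
- **CVR comparisons are confounded by age.** The Conclusions say signals are harder to obtain in older women, not that loss differs by arm. Loss that depends on age alone removes the guaranteed balance and leaves ordinary chance imbalance. Nor does the article list covariates for the secondary regressions, so age is not shown to be excluded there.

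**Conclusion.** The stated rationale is wrong and should go; its practical cost is conditional. If the two factors explain 10%, 20% or 30% of the variance of whatever is analysed, omitting them lowers the type I error to about 4%, 3 to 3.6% or 2.4 to 2.7% and costs about 2, 5 or 7 to 8 power points at 74 women. At 5% or less, the power difference is about one point or smaller. For the planned comparison of change, the explained share may be near zero.

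These figures rest on assumed R², a two-sided 5% test, banded minimisation, and 0.67 being expressed in SDs of the analysed outcome. This is a nearly free gain in efficiency and in the match between analysis and allocation. It is not a required correction.

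**What to change.** In section 2.14, delete the clause that uses minimisation as the reason to set the two factors aside. State instead that age and years since cessation of menses, both continuous as collected, are fixed covariates in the primary model and in the secondary regressions, including CVR, whatever their observed balance or correlation with the outcome.

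If the primary test is run as a two-visit repeated-measures model, let both covariates act on the change (that is, interact with time). A covariate main effect alone would not alter the treatment-by-time test.

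The cost is one sentence and two degrees of freedom (72 to 70 with 74 women). If the factors prove unrelated to the outcome, power moves only from 81.14% to 81.11% by formula. No new data are needed, and since section 2.3 keeps the blind until analysis is complete, the change can be made before unblinding.

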### 2.8. Transcranial Doppler Ultrasound Assessements

#### Basal Cerebral Haemodynamics

TCD is a non-invasive technique that utilises ultrasound to assess blood flow velocity in the brain. Using a TCD headpiece (Doppler-Box X, Singen, Germany), the MCA on both the left and right sides were isolated using the transtemporal window as this provides the least interference during insonation. The depth of insonation for MCA and PCA were between 45–60 mm and 60–70 mm respectively [34]. A 30-s of continuous recording of basal blood flow velocity in the MCA and PCA (maximum, minimum and mean) were obtained before hypercapnic provocation and before the start of each cognitive test. All basal blood flow velocities will be collated in spreadsheets and an average of the last 10 s of mean blood flow velocity (*x*) will be reported for use in CVR calculations. The pulsatility index (PI) of the MCA and PCA, reflecting stiffness in the cerebral vessels, is determined from the maximal velocity minus the minimum velocity and divided by the mean velocity obtained during basal conditions.

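### Basal PI, which needs a Doppler signal, may become a covariate in the primary cognitive analysis; an ordinary ANCOVA would then omit women with complete cognitive data but no PI

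*Protocol article*

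**What the plan says.** Section 2.14 (Statistical Analysis) defines the primary outcome as cognitive performance, "determined using a composite score of all memory tests". The model is given as: "Treatment by time effects will be determined by analysis of variance (ANOVA), or analysis of covariance (ANCOVA) in the event of interacting variables". After noting that minimisation handles age and years since menses, the section adds that "clinic BP, basal PI, BMI, 3MS score and years of education will be considered covariates if they were significantly correlated with the primary outcome".

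The source of PI is in section 2.8 (Basal Cerebral Haemodynamics): "The pulsatility index (PI) of the MCA and PCA, reflecting stiffness in the cerebral vessels", computed as maximum minus minimum velocity divided by mean velocity, all read from the TCD recording.

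On who has a signal, section 2.4 says "Those who met the eligibility criteria were fitted with a Transcranial Doppler (TCD) ultrasound headpiece", so Doppler comes after eligibility has been settled. Table 1 has no criterion for a usable signal. Section 3 (Conclusions) states that "the technical limitations of obtaining reliable TCD ultrasound signals, particularly in older women, did not warrant the inclusion of cerebrovascular function as the primary outcome", because recruitment might be limited.

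Section 2.2 gives the sample size: 74 women for 80% power at a standardised difference of 0.67 and p < 0.05, with 80 recruited to allow for attrition.

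**The concern.** Choosing a cognitive primary outcome means that a woman with no Doppler signal can be randomised, tested and analysed. The covariate rule in 2.14 can make the primary analysis depend on TCD again. Of the five listed covariates, only basal PI needs a Doppler signal. Blood pressure, height, weight and 3MS are obtained in section 2.4 before the headpiece is fitted, and years of education needs no device.

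If PI passes the correlation test and goes into a standard ANCOVA, a woman without a PI value contributes nothing to the treatment comparison, however complete her cognitive scores. Two things are at stake: the power of the primary test, whose only stated allowance is six women for attrition, and whom the result describes. By the article's own account, signal problems are more likely in older women, and the introduction motivates the trial by dementia risk in older women.

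**Working it through.** **Inputs from the article.** Standardised difference d = 0.67; 74 women needed, 80 recruited, 40 per group; p < 0.05.

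**Assumptions.** Two-sided test. The share of women without a PI value (f) is not given; 10%, 20% and 30% are used. Missing PI leads to omission, as in an ordinary ANCOVA. No other attrition in the main calculation.

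**Step 1: reproduce the plan's figure.** Two-sample t-test, exact noncentral t, noncentrality d × √(N/4), N − 2 degrees of freedom. The smallest equal-arm N reaching 80% is 72 (80.05%). At N = 74 power is 81.1% and at N = 80 it is 84.1%. The stated 74 is consistent with this to within two women.

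**Step 2: what PI must show to enter.** The correlation can be tested only in women who have PI. The smallest significant correlation at n women is r = c/√(n − 2 + c²), with c the two-sided 5% critical t on n − 2 degrees of freedom.

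| f | women with PI | entry threshold r | r² |
|---|---|---|---|
| 10% | 72 | 0.232 | 0.054 |
| 20% | 64 | 0.246 | 0.061 |
| 30% | 56 | 0.263 | 0.069 |

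**Step 3: power after the loss, crediting PI for precision.** A covariate with correlation r reduces the residual SD by √(1 − r²), so the effective difference is 0.67/√(1 − r²), with one further degree of freedom spent. At r = 0.30 this is 0.67/√0.91 = 0.702.

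| f | women analysed | power, r at threshold | power, r = 0.30 | power, no precision credit |
|---|---|---|---|---|
| 0, unadjusted | 80 | – | – | 84.1% |
| 10% | 72 | 82.2% | 83.6% | 80.0% |
| 20% | 64 | 77.7% | 79.0% | 75.1% |
| 30% | 56 | 72.3% | 73.2% | 69.2% |

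The last column is shown only for contrast. It describes a covariate that explains nothing, which the entry rule would normally screen out.

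**Step 4: break-even.** Information relative to the unadjusted full sample is (1 − f)/(1 − r²). It exceeds 1 only if f is below r². At r = 0.30 that means f below 9%. At f = 20% and r = 0.30 it is 0.80/0.91 = 0.88. To repay 10%, 20% or 30% loss, r must reach √f, about 0.32, 0.45 or 0.55.

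**The case against.** The strongest reply is that the article nowhere prescribes dropping women with missing PI. Handling of a missing baseline covariate is ordinarily left to a full protocol or SAP, and imputation there would remove the problem with 2.14 unchanged. This stands as a limit: silence on missing PI is not the finding. The finding is that 2.14 names, for the primary analysis, a covariate whose measurement the article itself regards as unreliable to obtain. Omission is the default behaviour of an ordinary ANCOVA, not a rule stated in the text.

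Other limits also stand. PI enters only if it correlates significantly, so the loss is possible, not certain. Nothing in the document anchors the failure rate. The text does not say which vessel or side supplies basal PI; a woman with one usable artery may still have a value, so PI could be missing less often than a full set of Doppler responses.

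Three stronger readings are tempting but not supported.

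- *That the omission unbalances the arms or undoes the minimisation on age.* PI is measured at baseline, before supplementation and under blinding, so its absence cannot depend on treatment. Losing older women shifts the population in both arms; it does not systematically separate them.
- *That the rule defeats the reason for choosing a cognitive primary outcome.* The reason given in section 3 is limited recruitment, and section 2.4 reports that the target of 80 was reached.
- *That power falls to 80%, 75% or 69%.* Those figures give PI no credit for precision, although it enters only when correlated with the outcome.

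**Conclusion.** The point holds in conditional form. If basal PI meets the entry rule and an ordinary ANCOVA is run, the primary comparison omits women whose cognitive data are complete. The harm is to precision and to the population described, not to the validity of the randomised contrast.

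The size depends on an unknown failure rate. At 10% missing the loss is small, and power stays above the planned 80% if there is no other attrition. At 20% it falls just below 80%, and at 30% clearly below. A failure fraction under about r² would make adjustment a net gain. These results assume d = 0.67, a two-sided test, correlations from the entry threshold to 0.30, and all 80 women otherwise evaluable; ordinary attrition would lower them further.

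This should be changed, but it does not threaten the trial. The article describes the analysis as still to come, so the change can be made before unblinding.

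**What to change.** In section 2.14, remove basal PI from the candidate covariates of the primary cognitive analysis. Keep the other four (clinic BP, BMI, 3MS score, years of education); none depends on Doppler, and this point gives no reason to drop them or to add others. Use PI in the cerebrovascular responsiveness analyses, or in a sensitivity analysis of the cognitive outcome among women with a signal.

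Alternatively, keep PI on the list and state that a missing baseline value is imputed and never excludes a woman from the primary analysis.

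Either change is one sentence and needs no new data. The cost of removal is whatever precision PI would have added; for scale, with PI available in all 80 women and r = 0.30, power would be 87.3% instead of 84.1%.

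### Covariates enter the primary model only if they correlate significantly with the trial's own primary outcome, at an unstated level and time point, instead of being fixed in advance

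*Protocol article*

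**What the plan says.** Section 2.14 of the protocol article is the only place that describes the primary model.

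- The primary outcome is cognitive performance, "determined using a composite score of all memory tests". It is tested by ANOVA for treatment by time, "or analysis of covariance (ANCOVA) in the event of interacting variables".
- Age and years since cessation of menses are taken to be balanced by minimisation and are not listed as covariates. Section 2.3 confirms that these are the two minimisation factors.
- The candidates for adjustment are "other baseline characteristics such as clinic BP, basal PI, BMI, 3MS score and years of education". They "will be considered covariates if they were significantly correlated with the primary outcome".
- "Statistical significance for the primary outcome is set at *p* < 0.05"; secondary outcomes get false discovery rate control.

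The article does not say at what level the correlation is judged, or which version of the primary outcome it is judged against. Section 2.3 keeps the blind until all data analysis is finished.

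**The concern.** A confirmatory model should be known before the outcome data are seen. Here the adjustment set follows from significance tests against the outcome that the trial is meant to test.

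The undefined time point matters. If the composite at baseline is meant, selection uses only pre-treatment data. If week 14 or change is meant, it uses post-randomisation data. A variable such as education may track the level of the composite but not its change, so the three readings can select different covariates.

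Significance is also a weak guide to usefulness at this sample size. A covariate worth adjusting for can fail the test by chance, and an irrelevant one can pass. Leaving out the minimisation factors adds to this: balancing a prognostic factor by design and then omitting it from the model leaves its variance in the error term.

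At stake are the precision of the single primary test and a reader's ability to confirm which model was planned.

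**Working it through.** **Inputs from the article.** Section 2.2: the power calculation "showed that 74 participants would give 80% chance of detecting a statistically significant difference" at a "medium effect size (standardized difference = 0.67) in cognitive performance (composite score"), and "To allow for attrition, we aimed to recruit 80 women". Section 2.14: alpha 0.05 and five named candidates. Section 2.4: 40 women per group.

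**Assumptions.** The article gives no correlation between any covariate and the composite, so a range is used. The test is taken as two-sided, the covariates as independent and normal, and the entry level as 0.05.

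**1. The plan's own figure.** A two-sample t-test with d = 0.67, two-sided alpha 0.05 and 80% power needs 35.96, so 36 per arm or 72 in total. With 37 per arm (74 in total) power is 81.1%. The stated 74 is reproduced within two women. It rests on an unadjusted comparison, so this point does not alter it.

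**2. How often the rule drops a useful covariate.** By Fisher's z, the standard error is 1/√(74 − 3) = 0.1187.
- r = 0.2: atanh(0.2) = 0.2027, and 0.2027/0.1187 = 1.71. The chance of reaching 1.96 is about 40%, so the covariate is dropped about 60% of the time.
- r = 0.3: atanh(0.3) = 0.3095, and 0.3095/0.1187 = 2.61. The chance is about 74%, so it is dropped about 26% of the time.

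**3. How often it admits an irrelevant one.** If none of the five is prognostic, the chance that at least one enters is 1 − 0.95⁵ = 22.6%.

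**4. Type I error** (null simulations, 74 women, five covariates; columns give the outcome variance explained by each covariate):

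| Way of choosing the model | 2% | 5% | 10% |
|---|---|---|---|
| Rule applied mechanically, closed list | 5.6% | 5.2% | 4.7% |
| Better of unadjusted and rule-selected | 6.9% | 7.5% | 7.5% |
| Best subset of the significant covariates | about 6–7% | about 9–10% | about 15–16% |
| Best of all 2⁵ = 32 subsets | about 9–10% | about 12–13% | about 19–21% |

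Across separate simulations the first row lay between 4.7% and 5.7%. With 4,000 runs the simulation error near 5% is √(0.05 × 0.95/4000) = 0.3 points. The 10% column assumes that the five covariates together explain 5 × 10% = 50% of the outcome variance.

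**5. Power at d = 0.67, 74 women:**

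| Correlation of each covariate | Rule | Fixed set | Difference (fixed − rule) |
|---|---|---|---|
| 0 (six covariates) | 79.7% | 77.3% | −2.4 |
| 0.2 (five covariates) | 83% | 86% | +3 |
| 0.2 (six covariates) | 83.2% | 87.2% | +4.0 |
| 0.3 (five covariates) | 92% | 96% | +4 |
| 0.3 (six covariates) | 93.7% | 97.9% | +4.2 |

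The six-covariate runs allow for one candidate beyond the five named. The fixed set had type I error of 4.8 to 5.1%.

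**The case against.** The strongest reply is that the rule is public, uses baseline variables and does not refer to treatment. Followed as written, it holds type I error at its nominal level. That stands.

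A reader might infer that the plan carries a 9 to 20% false-positive risk because five candidates allow 32 models. The article does not support this. The rule admits only significantly correlated covariates, and taking the best of 32 subsets would mean including ones that fail it. Even the loosest reading, in which the analyst is free to leave out qualifying covariates, gives lower figures. All of them also depend on assumed correlations.

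The blind in section 2.3 is a further safeguard. It prevents a choice that favours resveratrol knowingly. It would not prevent choosing the smallest two-sided p-value between coded groups, and it does not identify the planned model. It limits the risk without removing it.

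The open-ended list may be no more than condensation for a journal, with the full list held elsewhere, so little weight is placed on it. The entry rule is different: it is a positive statement of method, and an analysis plan that followed it would carry the same weakness.

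Finally, the precision loss is modest, and the rule does slightly better than a fixed set if no covariate is prognostic. That is correct. A null relation is, however, an unlikely case for a baseline composite in a cognitive trial.

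**Conclusion.** The point holds in a limited form. The primary model's covariates are chosen by significance against the primary outcome, with the entry level and time point undefined and the minimisation factors left out.

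This does not invalidate the test. Under mechanical use on a closed list, type I error stays near 5%. Nor does it show that the reported p-value would be an unplanned one, which a reader might also infer: for the named candidates, someone with the data could check which qualify once level and time point are settled.

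The cost is a confirmatory model that depends on the data, and about 3 to 4 points of power lost against a fixed set if covariates each correlate 0.2 to 0.3 with the outcome. Against that stands a gain of 2 to 3 points if none does. Inflation to about 9 to 20% is a worst case outside the stated rule. These sizes rest on assumed correlations, independent covariates, a two-sided test and 74 women analysed. The point is a cheap improvement that should be made.

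**What to change.** Before unblinding, replace the significance-based rule with a closed covariate set that is fitted whatever correlations are observed:

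- the baseline composite score, so that the treatment effect is read from a model of the week-14 (or, equivalently, change) score;
- the two minimisation factors, age and years since cessation of menses;
- any further prognostic baseline variables that the sponsor names in advance, for example years of education.

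Label every other adjustment as a sensitivity analysis, and delete the conditional switch between ANOVA and ANCOVA.

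The cost is a short change of wording and a few degrees of freedom in 74 to 80 women. The covariates are baseline values that the trial already collects, and the sample size does not change. The sponsor accepts a loss of 2 to 3 points of power in the unlikely case that none of the chosen variables is prognostic.
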